**Figure 2 figure2:**
[figure not shown]
*SavvyHER* study procedures. FGD: focus group discussion; RCT: randomized controlled trial; *SavvyHER*: Sexual/HIV Health Electronic Empowerment Resource.

### Data Collection

All assessments are taken through REDCap, a secure platform for constructing web-based surveys and databases [54]. Participant data is stored under a unique study ID number to ensure security and privacy. In order to inform intervention testing, we collect data on the number and yield of screened participants enrolled, recruiting sources that generated the largest number of enrolled individuals, effective recruitment used for successful enrollment, elapsed time from first contact to enrollment, amount of app interactions, and technological challenges or glitches. Feedback on content and delivery is elicited through REDCap surveys and focus group sessions or interviews, which both undergo qualitative data analysis, also known as coding. Additionally, we collect data on participants’ ownership of smartphones and preferred app formats. These measures will help determine the time, resources, and workload necessary for implementing the HIV prevention mobile app for Black women. Moreover, with this data, we can assess whether users perceived the app as beneficial and whether alternatives (in app content and delivery) can be determined.

All participants provide demographic information through REDCap surveys. Primary outcome measures focus on the feasibility, usability, and acceptability of the *SavvyHER* app in addition to the control group procedures. Feasibility metrics will be determined by meeting predefined benchmarks specific to retention, screening, and interaction with app features. Examples include the number of weekly app sign ins, time spent using the app, and its features. Usability and acceptability will be assessed with the system usability scale (SUS) and a 30- to 45-minute exit interview that queries participants’ experience with study procedures [55]. Because this is a feasibility study, we do not propose a statistical analysis of changes in behavior (eg, PrEP initiation, HIV testing) among users of the *SavvyHER* mobile app. Secondary measures collected in phase III include information on social determinants of health (eg, health care access near her location, employment status, housing status, transportation access, and social support), sexual health history and knowledge, self-perceived discrimination, mental health status, experiences of intimate partner violence, PrEP stigma, racism, and discrimination, personal media and technology use, as well as web-based health information seeking. The completion of the end line survey will also indicate the feasibility of study procedures (eg, retention). A summary of primary and secondary measures is displayed in Table 2.

**Table 2 table2:** *SavvyHER* study outcome measures.

Measure		Questionnaire or survey	Weekly survey	Baseline or end line survey
Demographics		Name, age, race and ethnicity, gender identity, county of residence, relationship status, education, household income	✓	✓
Social determinants of health and women’s sexual health history		Your current life situation [56,57] Protocol for responding to and assessing patients’ assets, risks, and experiences (PRAPARE) [58] A guide to taking a sexual history [59]		✓

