**Results:**

Findings from preliminary focus groups revealed educational content, app aesthetics, privacy considerations, and marketing preferred by Black women, thus informing the first functional *SavvyHER* prototype. As we adapt and test the feasibility of *SavvyHER*, we hypothesize that the app will be an effective, sustainable, and culturally relevant HIV prevention, sexual health, and reproductive wellness tool for Black women.

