**Secondary outcomes**				
	HIV knowledge	Human Immunodeficiency Virus- Knowledge Questionnaire (HIV-KQ AG) [62]		✓
	HIV risk	PrEPa information and self-screening tool for women [63]		✓
	HIV and PrEP stigma, PrEP intention or initiation	Brief HIV PrEP stigma scale (HPSS) [64]		✓
	Self-reported racial/ethnic discrimination	Everyday racial/ethnic discrimination scale [65]		✓
	Depression	Patient health questionnaire-2 (PHQ-2) [66] The patient health questionnaire (PHQ-9) [67]		✓
	Self-reported social media use and technology use; attitudes toward technology use	The media and technology usage and attitudes scale (MTUAS) [68]		✓
	Information seeking	Web-Based Health Information Seeking [69]		✓
	Usability assessment of *SavvyHER*	Health information technology usability evaluation scale (Health-ITUES) [70]		✓
	User experience of *SavvyHER*	User experience questionnaire [71] User experience questionnaire short from (UEQ-S) [71]		✓

^a^PrEP: pre-exposure prophylaxis.

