### Data Analysis Plan

#### Quantitative Analysis

Data will be downloaded from REDCap into STATA (StataCorp). Exploratory and descriptive analyses will be conducted for all study variables. Variables will be examined for normality in addition to means, SD, range, and medians. The literature on effect size estimates, from pilot studies and National Institutes of Health (NIH) recommendations, confirms that attempting to obtain valid estimates of effect sizes cannot be statistically justified [72-78]. We have identified feasibility and acceptability as the primary outcomes of this pilot. We have indicated target metrics that will substantiate feasibility, and we will use both quantitative survey and qualitative interview data to determine the acceptability of both the mobile app and the control condition. For all outcome measures (eg, PrEP knowledge), a mean score and 95% CI will be calculated, and distributional assumptions will be assessed. The mean change in outcome measure scores between pretest (T0) and posttest (T1) will be compared (paired samples *t* test) for trends in the expected direction or no change. A paired samples *t* test will be conducted to evaluate the mean change in outcome measure scores between pretest (T0) and posttest (T1) within groups. *t* Tests will also be used to compare variables before the intervention among the 2 groups. To compare differences between intervention and control groups, a 2-way analysis of covariance (ANCOVA) will be used in which covariates will be controlled for. All statistical tests will be performed at a 95% CI with an alpha of .05.

We will use mobile app analytics (eg, Google Analytics) to assess trends in app engagement, such as duration and number of app/module/social media forum engagement, clicks, modules viewed/completed, GPS solicitation, and correct or incorrect responses to questions. Analytics data will be collected as categorical and continuous variables. Continuous variables will be transformed into categorical variables, and multivariable logistic regression will be conducted to evaluate the relationship between usage characteristics and primary outcomes using STATA.

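### The pilot says effect sizes cannot be validly estimated, then specifies within-arm, baseline and between-arm significance tests at alpha .05, and lists PrEP initiation as an outcome after excluding its analysis

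*Protocol article*

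**What the plan says.** Four statements bear on this point.

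- **Data Collection.** Because this is a feasibility study, "we do not propose a statistical analysis of changes in behavior (eg, PrEP initiation, HIV testing").
- **Quantitative Analysis, rationale.** For pilots, "attempting to obtain valid estimates of effect sizes cannot be statistically justified". Feasibility and acceptability are named as primary, with target metrics.
- **Quantitative Analysis, methods (same paragraph).** "For all outcome measures (eg, PrEP knowledge), a mean score and 95% CI will be calculated". Paired t tests on pre-to-post change are to be looked at for movement in the hoped-for direction or none, and a paired test "will be conducted to evaluate the mean change in outcome measure scores between pretest (T0) and posttest (T1) within groups". The two groups are also compared by t test before the intervention, and an ANCOVA compares the arms. Finally, "All statistical tests will be performed at a 95% CI with an alpha of .05".
- **Table 2, secondary outcomes.** One row is labelled "HIV and PrEP stigma, PrEP intention or initiation". The only instrument named in it is the "Brief HIV PrEP stigma scale (HPSS) [64".

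The Abstract (Results) adds that "we hypothesize that the app will be an effective, sustainable, and culturally relevant HIV prevention" and sexual health tool.

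**The concern.** The rationale and the methods point in different directions. A plan that holds effect estimation from a pilot to be unjustified has no stated use for a set of alpha .05 tests on outcome scores, yet it specifies them and does not say how a significant result should be read. With an effectiveness hypothesis stated in the Abstract, a chance p value below .05 has a ready claim to attach to.

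Separately, the analyst cannot tell what to do with PrEP initiation. One section names it as a behaviour whose change will not be analysed statistically. The outcome table lists it beside scores that will be.

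**Working it through.** **1. The passages side by side.**

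| Topic | Rationale | Methods or table |
|---|---|---|
| Effect sizes | Valid estimates not justifiable | Between-arm ANCOVA at alpha .05 |
| Primary aim | Feasibility and acceptability | Within-arm change tested and read for direction |
| PrEP initiation | No statistical analysis of change | Listed as a secondary outcome; instrument named is a stigma scale |

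The first two conflicts lie within one paragraph. The third needs Data Collection and Table 2 to be read together.

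**2. Number of between-arm tests.** Table 2 has nine secondary rows. Two (Health-ITUES and user experience) concern the app itself, so the control arm cannot answer them: 9 − 2 = 7. One between-arm test per row is my assumption; the article gives no count.

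**3. Chance positives between arms.** With k independent true nulls, P(at least one p < .05) = 1 − 0.95^k, and the expected number is 0.05k.

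- k = 7: 1 − 0.698 = 0.302; expected number 0.35.
- k = 5 (leaving out discrimination and media use, which few would read as app effects): 1 − 0.774 = 0.226.
- k = 9 (all rows): 1 − 0.630 = 0.370.

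Positive correlation among outcomes would lower these probabilities but not the expected number.

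**4. Detectable difference.** The stated size is 60, or 30 per arm. It was set by feasibility aims and a rule of 10-20 participants per concept, not by power. It cannot be reproduced, because neither the number of concepts nor the attrition allowance is given. For a two-sided .05 test (sidedness assumed), the normal approximation is d = (1.960 + 0.842) × √(2/n).

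- n = 30: 2.802 × 0.258 = 0.72 SD; the t-based value is 0.74 SD.
- n = 24 (20% loss, the share lost in phase II, where 8 of 10 completed): 2.802 × 0.289 = 0.81 SD; t-based 0.83 SD.
- t-based power at d = 0.5 is about 48% with 30 per arm and 40% with 24.

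Baseline adjustment helps by a factor √(1 − r²). With an assumed correlation r = 0.5 this is 0.866, so 0.74 becomes 0.64 SD.

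**5. Within-arm tests.** Mean change in the app arm is the app effect plus time, retest and other common influences. A paired t test asks whether that sum is zero and cannot isolate the app effect. Only the between-arm contrast removes what the arms share.

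**6. Baseline tests.** After proper randomisation, any baseline difference is due to chance, so a significance test answers no question the pilot has.

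**7. Precision if only estimates are reported.** The unadjusted 95% CI half-width is 2.00 × √(2/30) = 0.52 SD at 30 per arm. That shows plainly the imprecision the rationale acknowledges.

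**The case against.** The best defence is that nothing rides on these tests. Feasibility and acceptability are primary, no progression rule uses a p value, the article announces no efficacy claim, and its analysis section opens by promising exploratory and descriptive analyses of all variables. Most of this stands, and it limits the severity. But that opening line is general and does not label the later alpha .05 tests as exploratory.

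A second objection is that an adjusted difference with a 95% CI is itself an effect estimate, and that an interval excluding zero is the same event as p < .05. This is correct. Removing p values alone would change only the label, so the intervals must be marked as planning information and not read as tests against zero.

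Several stronger readings are tempting but unsupported:

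- **That every outcome measure is to be tested within and between arms.** The wording about all outcome measures governs only means and CIs. The paired-test sentences speak of outcome scores, and the ANCOVA sentence names no outcome.
- **That the Data Collection exclusion forbids all this testing.** It covers behaviours. Testing knowledge, stigma or depression scores does not contradict it; only PrEP initiation does.
- **That false positives number in the dozens of tests.** Three tests for each of seven rows gives 21 and 1 − 0.95^21 = 66%; adding seven baseline tests gives 28 and 76%. But control-arm paired tests and baseline tests cannot produce a false claim that the app works.
- **That intention and initiation are not collected.** The scale's items are not in the article, so its content is known only by name. The sexual-history guide or the PrEP self-screening tool might carry such items, though Table 2 does not assign them to this row.
- **That the larger trial is deprived of its outcome.** The article does not define that trial's outcome.

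**Conclusion.** The inconsistency is real and should be fixed before analysis, though it does not threaten the design, the primary outcomes or the sample size. The tests as specified do not fit the plan's own rationale, carry no multiplicity control and come with no statement that they are not evidence of efficacy.

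The chance of at least one false between-arm positive is about 30%, with a range of 23% to 37% across five to nine rows. This assumes one test per row, true nulls and independence. The detectable difference of about 0.74 SD assumes 30 per arm, two-sided testing and no gain from baseline adjustment. The points on within-arm tests and on PrEP initiation rest on no numerical assumption.

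**What to change.** 1. Delete the alpha .05 sentence and the within-arm and baseline significance tests.
2. For each secondary score, report arm means and the baseline-adjusted between-arm difference with a 95% CI and no p value. State that these are planning information, not evidence of effect, and that the intervals are not to be read as tests against zero.
3. State that progression rests only on the feasibility and acceptability benchmarks.
4. Reconcile Data Collection, Table 2 and Quantitative Analysis on PrEP initiation: either report it descriptively as counts by arm and name the survey item that captures it, or remove it from Table 2.

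The cost is a few sentences, possibly one survey item if none exists, and the loss of p values that the plan's own rationale does not support.

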**Primary outcomes**				
	Usability/acceptability	System Usability Scale (SUS) [60,61]	✓	✓
	Feasibility	Average number of app sign ins per week; number of minutes spent using the app weekly; sexual health tracking entry, home test kit ordering, number of app glitches; 40% of participants using My Logger, My Test, My Resources and My Circle		✓
**Secondary outcomes**				
	HIV knowledge	Human Immunodeficiency Virus- Knowledge Questionnaire (HIV-KQ AG) [62]		✓
	HIV risk	PrEPa information and self-screening tool for women [63]		✓
	HIV and PrEP stigma, PrEP intention or initiation	Brief HIV PrEP stigma scale (HPSS) [64]		✓
	Self-reported racial/ethnic discrimination	Everyday racial/ethnic discrimination scale [65]		✓
	Depression	Patient health questionnaire-2 (PHQ-2) [66] The patient health questionnaire (PHQ-9) [67]		✓
	Self-reported social media use and technology use; attitudes toward technology use	The media and technology usage and attitudes scale (MTUAS) [68]		✓
	Information seeking	Web-Based Health Information Seeking [69]		✓
	Usability assessment of *SavvyHER*	Health information technology usability evaluation scale (Health-ITUES) [70]		✓
	User experience of *SavvyHER*	User experience questionnaire [71] User experience questionnaire short from (UEQ-S) [71]		✓

^a^PrEP: pre-exposure prophylaxis.

### Data Analysis Plan

#### Quantitative Analysis

Data will be downloaded from REDCap into STATA (StataCorp). Exploratory and descriptive analyses will be conducted for all study variables. Variables will be examined for normality in addition to means, SD, range, and medians. The literature on effect size estimates, from pilot studies and National Institutes of Health (NIH) recommendations, confirms that attempting to obtain valid estimates of effect sizes cannot be statistically justified [72-78]. We have identified feasibility and acceptability as the primary outcomes of this pilot. We have indicated target metrics that will substantiate feasibility, and we will use both quantitative survey and qualitative interview data to determine the acceptability of both the mobile app and the control condition. For all outcome measures (eg, PrEP knowledge), a mean score and 95% CI will be calculated, and distributional assumptions will be assessed. The mean change in outcome measure scores between pretest (T0) and posttest (T1) will be compared (paired samples *t* test) for trends in the expected direction or no change. A paired samples *t* test will be conducted to evaluate the mean change in outcome measure scores between pretest (T0) and posttest (T1) within groups. *t* Tests will also be used to compare variables before the intervention among the 2 groups. To compare differences between intervention and control groups, a 2-way analysis of covariance (ANCOVA) will be used in which covariates will be controlled for. All statistical tests will be performed at a 95% CI with an alpha of .05.

We will use mobile app analytics (eg, Google Analytics) to assess trends in app engagement, such as duration and number of app/module/social media forum engagement, clicks, modules viewed/completed, GPS solicitation, and correct or incorrect responses to questions. Analytics data will be collected as categorical and continuous variables. Continuous variables will be transformed into categorical variables, and multivariable logistic regression will be conducted to evaluate the relationship between usage characteristics and primary outcomes using STATA.

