#### Phase III: *SavvyHER* Pilot Feasibility Trial

After the *SavvyHER* app is refined and optimized using feedback from phase II under the guidance of the CAB, we will evaluate the feasibility, acceptability, and usability of the *SavvyHER* app through a pilot feasibility trial in phase III. This intervention will include a total of 60 Black women who will be recruited and randomized into the intervention group (N=30) or the control group (N=30). The sample size was determined based on feasibility objectives and measures and general guidelines for path analysis, which recommend a sample size of 10-20 participants per study concept while accounting for attrition. Interested participants will provide their contact information, and a research team member will follow up with a baseline assessment and group assignment. After baseline assessments are completed, participants will be randomized 1:1 to either intervention or control using a randomization schedule generated by our statistician using a permuted block procedure [52]. Allocation concealment will be employed before the randomization of participants. Once participants are assigned to groups, blinding will occur, in which researchers involved in data analysis will be blinded to the groups in which participants are enrolled to reduce observer bias and bias in data analysis and interpretation [53]. To restrict access to the *SavvyHER* app to the intervention group, participants will be provided with a single-use registration code that will need to be entered to gain access to the app. Study team members will teach participants how to download the app and navigate app features such as reminders.

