Each participant will have 4 months to engage with the app, with e-reminders at time intervals preferred by the participants (a minimum of 3 times per week) through push notifications. We will ask that participants schedule reminders during their peak times of cell phone use. Participants will also be prompted to take a weekly survey to provide app feedback similar to the weekly survey in phase II. Research staff will complete 2-month check-ins through phone call or video chat with participants in both the intervention and control conditions. At month 4, all participants will complete an endline survey in addition to an exit interview. Procedures for exit interviews are the same as those used in phase II. Participants will be remunerated for completion of the baseline assessment and for completion of the endline survey and exit interview. Furthermore, the CAB will review all feedback given and deliberate on what improvements or changes should be made to the *SavvyHER* app.

The control condition will be a 1-time web-based women’s health counseling session with a health care provider. Participants will be given information on (1) STI and HIV prevention; (2) family planning; and (3) general health promotion (eg, exercise and diet). The control condition provides access to HIV prevention materials that are publicly available but that do not offer the dynamic and individually customized features of the health communication and new media research approach proposed herein. The control group will not have access to the *SavvyHER* app until after the study has concluded. See Figure 2 for a visual depiction of *SavvyHER* study procedures.

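### The planned logistic regression of primary outcomes on app usage sets usage against itself for the usage-based feasibility metrics, and for the SUS it dichotomizes a score in at most 30 app users

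*Protocol article*

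**What the plan says.** The last paragraph of Quantitative Analysis in the protocol article describes an engagement analysis based on app analytics. The example variables are "duration and number of app/module/social media forum engagement, clicks, modules viewed/completed, GPS solicitation, and correct or incorrect responses to questions". Two steps follow. First, "Continuous variables will be transformed into categorical variables". Second, "multivariable logistic regression will be conducted to evaluate the relationship between usage characteristics and primary outcomes".

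Table 2 lists two primary outcomes. Usability/acceptability is measured by the SUS. The feasibility entry begins "Average number of app sign ins per week; number of minutes spent using the app weekly" and goes on to tracking entries, test-kit orders, glitches and a 40% benchmark for use of the four app features. The Data Collection text adds retention and screening benchmarks.

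Phase III participants are "randomized into the intervention group (N=30) or the control group (N=30"), and the section also says "The control group will not have access to the *SavvyHER* app until after the study has concluded". Usage data in the trial can therefore come only from the 30 women allocated to the app.

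**The concern.** The plan commits to a particular transformation and a particular model, and both fit the design poorly.

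- **Usage-based feasibility metrics.** The outcome and the predictors are the same kind of log data. A finding that women with longer app duration spend more minutes in the app carries no information.
- **SUS.** The question is sensible, but the chosen model discards information on both sides in a very small sample. With several categorized predictors it is also sparse.

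The pilot is meant to prepare a larger trial. Tautological or unstable odds ratios could influence which features are kept. The same section also argues that a pilot cannot support valid effect-size estimates, and adjusted odds ratios from 24 to 30 women would be estimates of that kind.

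**Working it through.** **The plan's own figure.** The total of 60 is attributed to feasibility aims and "general guidelines for path analysis, which recommend a sample size of 10-20 participants per study concept while accounting for attrition". Dividing, 60/20 = 3 and 60/10 = 6, so 60 corresponds to 3 to 6 concepts before attrition. Neither the number of concepts nor the attrition rate is given, so the figure can be neither reproduced nor refuted. No sample size or power is stated for the logistic regression.

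**Step 1: overlap of outcome and predictor.**

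| Primary outcome component | Counterpart among the analytics variables | Same quantity on both sides? |
|---|---|---|
| Weekly sign-ins | Number of app engagements | Yes |
| Weekly minutes | Duration of engagement | Yes |
| Use of the four features | Number of module and forum engagements | Yes |
| Glitch count | None | No |
| Retention, screening | None | No |
| SUS | None | No |

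Tracking entries and kit orders are also in-app actions, though the analytics list does not name them. The 40% feature-use criterion applies to the group and is not a binary outcome for an individual woman.

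**Step 2: women available.** Only the app arm has usage data, so n is at most 30. The Study Design section analyses phases separately, so phase II users add none. If the phase II completion of 8 of 10 (Results) repeats, which is an assumption, n = 30 × 0.8 = 24.

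**Step 3: cost of cutting, for SUS against one usage metric.** Assumptions: bivariate normal variables, both split at the median, two-sided alpha 0.05. After the split the correlation becomes phi = (2/π)·asin(r). Power ≈ Φ(atanh(ρ)·√(n−3) − 1.96), with ρ = r if both stay continuous and ρ = phi if both are split.

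- r = 0.5, n = 30, continuous: 0.549 × 5.196 − 1.96 = 0.89, power 81%.
- r = 0.5, n = 30, split: phi = 0.333; 0.347 × 5.196 − 1.96 = −0.16, power 44%.
- r = 0.4, n = 30, continuous: 0.424 × 5.196 − 1.96 = 0.24, power 60%.
- r = 0.4, n = 30, split: phi = 0.262; 0.268 × 5.196 − 1.96 = −0.57, power 29%.

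The 81% is for a Pearson correlation. In simulation, Spearman gave 76% at n = 30 and 66% at n = 24 for r = 0.5.

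**Step 4: events per predictor.** Assumptions: all six listed characteristics enter one model, each binary, with a 40% event rate.

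- n = 30: 30 × 0.40 = 12; 12/6 = 2.0.
- n = 24: 24 × 0.40 = 9.6; 9.6/6 = 1.6.
- Best case at n = 30, a 50% event rate: 15/6 = 2.5.
- Three levels each (12 parameters), n = 30, 40%: 12/12 = 1.0.

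**Step 5: separation (no finite maximum-likelihood estimate).** Simulated with no true effects, a 40% outcome, six predictors and an assumed correlation structure of 0.3:

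| n | Binary predictors | Three-level predictors |
|---|---|---|
| 30 | about 4% | about 40% |
| 24 | about 16% | about 80% |

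**Step 6: one binary predictor, 15 v 15.** Power is 82% for 25% v 75% (OR 9) but 19% for 40% v 60% (OR 2.25). At a 50% outcome rate each cell holds 7.5, so the standard error of the log OR is √(4/7.5) = 0.73. The 95% CI then extends by a factor of exp(1.96 × 0.73) ≈ 4.2 either side.

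**The case against.** Much of the case for leaving the plan alone is fair.

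- **Circularity.** A reader might infer that the whole regression is circular. The documents do not support that. The SUS and glitch count are not usage metrics. Retention is naturally binary and needs no cutting, and relating it to engagement would not be tautological.
- **Number of predictors and cut-points.** The analytics variables are introduced as examples, and nothing says that all six enter one model. Cut-points, selection of predictors and exploratory labelling may stand in an analysis plan that is not shown, so their absence is no defect. The decision to cut, however, is stated.
- **The 40% rate.** It is borrowed from the feature-use benchmark. The article gives no SUS cut-off or event rate, so 2 events per predictor is illustrative.
- **False positives.** A reader might count the roughly 25% chance of at least one p<.05 among six null predictors against the logistic model. It is ordinary multiplicity: 1 − 0.95^6 = 26%. Six Spearman tests would share it.
- **Separation.** At n = 30 with binary predictors it is only a few percent. The high rates need three-level predictors or a rarer outcome, or, more moderately, attrition.
- **Importance.** Feasibility is judged by benchmarks, and acceptability by survey and interview data. This model is ancillary.

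What remains is usage regressed on usage, avoidable loss of information for the SUS, and too few women for a model with several predictors.

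**Conclusion.** The point holds in a limited form and should be fixed, but it does not threaten the trial's main conclusions. For sign-ins, minutes and feature use, the regression returns associations by construction; this needs no assumption beyond the document's own definitions. For the SUS, the logistic model requires dichotomizing a continuous score in at most 30 women. The fall in power from about 81% to about 44% at r = 0.5 assumes that both variables are split at the median and that no woman is lost. The figure of about 2 events per predictor assumes six binary predictors in one model and a 40% event rate. The number 24 assumes that phase II completion repeats. Other cut-points, fewer predictors or another event rate would change these sizes. They would not remove the need to cut the SUS or raise the number of women above 30.

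**What to change.** - Remove the categorization step and the multivariable logistic regression from Quantitative Analysis.
- Report each usage metric descriptively as a feasibility result, with 95% CIs, for all women randomized to the app, counting non-users as zero.
- For usage against usability, name one or two continuous usage metrics in advance. Relate each to month-4 SUS, kept as a score, in the app arm only (for example a Spearman correlation with a 95% CI), and label this exploratory. Keeping to one or two also limits the multiplicity: 1 − 0.95² ≈ 10% for two independent tests, against 26% for six.
- State that usage-based feasibility metrics will not be regressed on usage.

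The cost is a change of wording and the loss of adjusted odds ratios for presentation. Data collection, sample size and participant burden are unchanged. The replacement will still be imprecise: by Fisher's z for a Pearson correlation of 0.5 at n = 30, the limits are tanh(0.549 ± 1.96/5.196), about 0.17 to 0.73. The report should say so.
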